### Plans for collection, laboratory evaluation and storage of biological specimens for genetic or molecular analysis in this trial/future use {33}

Laboratory technicians certified in Nepal will collect 5 mL of venous blood sample at the baseline and endline from all participants. HbA1c and lipid panels (total cholesterol, LDL cholesterol, HDL cholesterol, and triglyceride) will be assessed for all participants while fasting plasma glucose will be additionally measured for those who had fasting fingerprick glucose ≥100 mg/dL. All samples will be analyzed following the reference method approved by the International Federation of Clinical Chemistry and Laboratory Medicine (IFCC). All specimens will be properly disposed of after completion of tests. No genetic or molecular analyses are planned for this trial or any ancillary studies.

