## Statistical methods

### Statistical methods for primary and secondary outcomes {20a}

The primary analysis will follow an intention-to-treat approach, comparing the mean differences in changes in systolic blood pressure, fasting plasma glucose levels, and changes in smoking status between individuals assigned to the intervention arm vs control arms. Primary outcomes will be measured at baseline and six months, requiring models that account for repeated measures and the hierarchical structure of participants nested within sites. To compare changes between groups, we will use mixed-effects models for each outcome: linear mixed-effects models for continuous outcomes (SBP, fasting blood glucose) and a mixed-effects logistic regression for the binary outcome (smoking status), each including a random intercept for participants. Fixed effects will include intervention, time (baseline and 6 months), their interaction, and potential confounders. For continuous outcomes, the interaction term represents the difference in mean change between groups. For the binary outcome, it represents the difference in change in log-odds of smoking cessation, with the odds ratio indicating how much greater (or smaller) the change in odds of cessation is for the intervention group relative to control.

Although outcomes may be correlated, the univariate approach is conservative and simplifies interpretation without assuming a multivariate distribution. Sensitivity analyses will use multivariate models accounting for correlations between outcomes. Continuous outcomes will be analyzed jointly using repeated-measures MANOVA or a multivariate linear mixed model with an unstructured covariance matrix. For mixed outcome types, a multivariate logistic mixed model or joint modeling approach will be applied. These models account for both outcome correlations and data hierarchy, allowing estimation of overall intervention effects and assessment of robustness relative to univariate analyses.

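### The multivariate sensitivity analyses permit a MANOVA that, as specified, ignores ward clustering, and a logistic model that does not fit continuous outcomes, while claiming that all options respect the data hierarchy

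*Protocol article*

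**What the plan says.** The Protocol article, under Statistical methods for primary and secondary outcomes {20a}, first sets a requirement: outcomes are measured at baseline and six months, "requiring models that account for repeated measures and the hierarchical structure of participants nested within sites". The primary analyses are separate mixed models for each outcome, "each including a random intercept for participants". The joint analyses come second: "Sensitivity analyses will use multivariate models accounting for correlations between outcomes".

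Two sentences then name the methods. For SBP and glucose: "Continuous outcomes will be analyzed jointly using repeated-measures MANOVA or a multivariate linear mixed model with an unstructured covariance matrix". For continuous and binary outcomes together: "For mixed outcome types, a multivariate logistic mixed model or joint modeling approach will be applied". One statement covers the whole set: "These models account for both outcome correlations and data hierarchy". The section gives these analyses the job of testing how robust the univariate results are. It gives no rule for choosing between the alternatives in either sentence.

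**The concern.** Two of the four named options do not match the job.

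- **Repeated-measures MANOVA** handles correlated outcomes and repeated measurements within a person. In its standard form, however, each participant is an independent unit and there is no term for the ward. Wards are the randomised units, so the statement that these models account for the hierarchy is wrong for this option.
- **A multivariate logistic mixed model** can carry random effects, so hierarchy is not its problem. Its problem is outcome type. It models binary responses, while two of the three primary outcomes, SBP and FPG, are continuous. They would have to be dichotomised, and the section neither says so nor gives cut-points.

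If the MANOVA branch were used, its standard errors would tend to be too small. Its agreement with the primary result would then be weaker evidence of robustness than it appears. This is more than detail left for later, because the article names a method and gives it a property that it lacks.

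**Working it through.** **1. The options side by side**

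| Option named | Continuous SBP, FPG | Binary abstinence | Ward clustering |
|---|---|---|---|
| Repeated-measures MANOVA | yes | no | none as specified |
| Multivariate linear mixed model | yes | no | yes, if a ward effect is specified |
| Multivariate logistic mixed model | only if dichotomised | yes | yes, if a ward effect is specified |
| Joint modelling | yes | yes | yes, if a ward effect is specified |

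**2. The plan's own clustering arithmetic (Sample size {14})**

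Inputs: 15 clusters per arm, ICC 0.01, COV 0.65, alpha 0.05/3 = 0.0167 and power 90%. SBP has SD 15.46 and difference 5; glucose has SD 45.5 and difference 26. Two-sided testing is assumed, because the article does not state it.

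Individual n per arm = 2 × [SD × (2.394 + 1.282) / difference]². Design effect DE = 1 + [(1 + COV²) × m − 1] × ICC.

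- SBP, m = 23: DE = 1 + (1.4225 × 23 − 1) × 0.01 = 1.317. n = 258.3 × 1.317 = 340 per arm, and 340/15 = 22.7, so 23 per ward (345 per arm). This matches the plan.
- Glucose, m = 6: DE = 1 + (1.4225 × 6 − 1) × 0.01 = 1.075. n = 82.7 × 1.075 = 89 per arm, and 89/15 = 5.9, so 6 per ward (90 per arm). This matches the plan.

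The plan therefore treats ward clustering as material: it adds about 32% to the SBP sample.

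**3. Single-outcome test that ignores wards**

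Actual type I error = 2 × [1 − Φ(z / √DE)]. This takes ICC 0.01 to apply to change from baseline, which the article does not say.

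| Per ward | DE | Nominal 0.05 (z = 1.960) | Nominal 0.0167 (z = 2.394) |
|---|---|---|---|
| 6 | 1.075 | 0.059 | 0.021 |
| 23 | 1.317 | 0.088 | 0.037 |

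MANOVA needs SBP and FPG from the same people. The article does not say how many will have both, so the two planning cluster sizes are used as a range.

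**4. Two-outcome MANOVA, simulated under no effect**

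With two time points, the arm-by-time test is Hotelling's T² on the two change scores. Settings were 15 wards per arm, cluster-size COV 0.65, an assumed correlation of 0.3 between outcomes, and 4,000 runs per setting. The Monte Carlo standard error near 0.0167 is √(0.0167 × 0.9833 / 4000) = 0.002. Rejection rates at nominal 0.0167:

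| ICC of change | 6 per ward, ward ignored | 23 per ward, ward ignored |
|---|---|---|
| 0 | 0.019 | 0.012 |
| 0.01 | 0.022 | 0.043 |
| 0.02 | 0.028 | 0.074 |
| 0.05 | 0.045 | 0.200 |

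At these two cluster sizes, the same test on ward means stayed between about 0.011 and 0.022 at every ICC tried.

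**The case against.** The strongest reply is that both sentences are alternatives and each contains a sound choice. A multivariate linear mixed model can hold a ward effect, and joint modelling can combine continuous and binary outcomes. The section itself demands models for nested data, and choosing among named sensitivity methods is ordinary SAP work. This stands as far as it goes, and it is why the point is small. It does not rescue the sentence that credits every option with handling the hierarchy, and nothing in the text rules out the unsuitable branch.

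The documents do not support four stronger readings that a reader might infer:

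- **MANOVA can never respect clustering.** Run on ward-level summaries, or with ward within arm as the error term, it does, and the ward-mean simulation shows this. The fault lies in the specification, which mentions neither.
- **Type I error reaches about 10%.** Putting 30 per ward into the formula gives DE 1.417 and 10.0% at nominal 5%. But 30 is the smoking cluster size, smoking is not in the MANOVA, and the article does not state the 0.65 COV for smoking.
- **MANOVA would delete participants whose glucose improves.** The specimen section {33} says that "fasting plasma glucose will be additionally measured for those who had fasting fingerprick glucose ≥100 mg/dL". This may refer to the screening test, since the same threshold is part of the diabetes definition in Eligibility criteria {10}. If it does apply at endline, the values are missing from the primary model and from the recommended joint models too. That is a separate measurement question.
- **The sensitivity results would be meaningless.** Ignoring a small ICC mainly affects standard errors and does not by itself bias the estimated difference. Stable ward differences also cancel in change scores, so inflation needs wards to differ in change.

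**Conclusion.** The point holds in limited form. The hierarchy claim is wrong for participant-level repeated-measures MANOVA, and the multivariate logistic mixed model is the wrong class for a set that includes continuous SBP and FPG.

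With an ICC of 0.01 for change, the excess type I error runs from slight at the glucose planning cluster size to about two and a half times nominal (0.043/0.0167 = 2.6) at the SBP size. That size rests on three assumptions: the ICC for change, the unknown number of people with both measurements, and two-sided testing. With no ward variation in change the excess disappears.

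No primary conclusion depends on these analyses, so this is a minor but clear correction.

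**What to change.** In Statistical methods {20a}:

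- Delete repeated-measures MANOVA, or restrict it explicitly to ward-level summaries.
- Delete the multivariate logistic option for mixed outcome types.
- For SBP and FPG, specify a multivariate linear mixed model with ward and participant random effects. Name the ward effect, because the only random effect the section names is the participant intercept.
- For all three outcomes, specify a joint mixed model (Gaussian for SBP and FPG, Bernoulli for abstinence) that includes a ward effect.
- Keep the sentence on outcome correlation and hierarchy only once it is true of every model listed.

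The cost is protocol or SAP wording, with no change to data collection or sample size. The one drawback is that the joint model may need a simplified covariance structure to converge, so a fallback structure should be stated in advance.

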### Interim analyses {21b}

Interim analysis for efficacy will be done at 3 months. Given the low-risk nature of this study, there will be no stopping guidelines established.

### Methods for additional analyses (e.g. subgroup analyses) {20b}

Exploratory subgroup analyses will be conducted by sex, age categories, socioeconomic status (including education level), hypertension stage, HbA1c stage, and smoking level. Analyses will be stratified if effect modification is observed and adjusted for potential confounders. Additional exploratory analyses may be conducted as appropriate based on emerging findings.

### Methods in analysis to handle protocol non-adherence and any statistical methods to handle missing data {20c}

Exploratory sensitivity analysis will be performed by comparing analyses conducted on intention-to-treat population vs per-protocol (i.e. adherent) population. For any variable in the final dataset that has more than 5% missing values, a series of sensitivity analyses will be performed, such as comparing analyses conducted on complete cases vs those conducted using an appropriate imputation framework.

### Plans to give access to the full protocol, participant level-data and statistical code {31c}

The full study protocol, de-identified participant-level dataset, and statistical code will be made available by the corresponding author upon reasonable request and subject to approval by the study team and relevant committees.

## Oversight and monitoring

### Composition of the coordinating center and trial steering committee {5d}

The coordinating center will be established in Pokhara Metropolitan City, Nepal, at the Nepal Development Society (NeDS) Pokhara office. It will be responsible for training research staff and FCHVs, supporting data management and responding to any safety concerns (e.g., adverse events) arising from study sites. The coordinating center will be served by full-time NeDS officers with bachelor’s or higher degrees in health science related fields. The data management team will be jointly comprised by a few data managers in the coordinating center as well as a data manager in JHSPH. Endpoint adjudication will not be performed. An independent Technical Advisory Board (TAB) will also be established, comprising of a diabetologist, cardiologist, public health researcher, health policy expert, and community health experts, which will provide overall supervision of the trial, ensuring the trial is conducted to high scientific, ethical, and regulatory standards. The TAB will meet once before the enrolment and twice during the trial. Day-to-day trial operations will be managed through regular meetings between the coordinating centre and JHSPH, held at least weekly and more frequently as needed.

### Composition of the data monitoring committee, its role and reporting structure {21a}

An independent Data Safety Monitoring Board (DSMB) will be established, comprising of an epidemiologist, biostatistician, cardiologist, and public health experts. The DSMB will be responsible for monitoring participant safety and the integrity of trial data, with a focus on detecting harm or benefit early. The board will be given an unblinded and deidentified dataset upon request to the PI and will receive all reporting on adverse events and serious adverse events, using a reporting template approved by the DSMB themselves.

The DSMB will convene a total of three times; before the enrolment, half-way through the trial, and at the endline of the trial.

### Adverse event reporting and harms {22}

Any unanticipated adverse or serious adverse events to participants will be reported to the JHSPH IRB, Nepal Health Research Council (NHRC) IRB, and the DSMB.

### Frequency and plans for auditing trial conduct {23}

Formal auditing procedures will not be conducted for this trial.

### Plans for communicating important protocol amendments to relevant parties (e.g. trial participants, ethical committees) {25}

Any major protocol amendments will be reported to clinicaltrial.gov registration and submitted for approval to both the JHSPH IRB and the NHRC IRB prior to implementation. Once approved, such changes will be communicated with trial participants by research staff in Nepal.

### Dissemination plans {31a}

The trial findings will be disseminated to scientific communities via peer-reviewed journal publications and conference presentations. They will also be disseminated to community members (including participants), health care professionals, and policymakers in Nepal via dissemination meetings and other platforms such as press conference and media outreach in Nepal.

## Discussion

To the best of our knowledge, this is the first trial to evaluate the effectiveness of task-sharing with CHWs in managing multiple cardiovascular disease (CVD) risk factors concurrently—hypertension, diabetes, and tobacco use—at scale in an urban LMIC setting. While CHWs have played a pivotal role in rural primary health care systems, their potential to deliver integrated NCD services in urban settings remains largely underexplored.

This trial offers important new insights by shifting the geographic and contextual focus of CHW-led interventions to urban areas. Most prior task-sharing studies involving CHWs have been conducted in rural LMIC settings, where they often served as the sole point of access to essential health services. However, urban populations present distinct challenges and opportunities—such as competing providers from non-governmental healthcare systems, high population density, and a wider range of health risks, including greater exposure to ultra-processed food and sedentary lifestyles. These conditions introduce greater variability in both individual-level health needs and health system-level coordination, which must be accounted for when designing and evaluating public health interventions. By embedding this trial in Pokhara Metropolitan City, a rapidly urbanizing metropolitan city in Nepal, this study will help assess whether task-sharing with CHWs remains effective in more complex, densely populated health system contexts.

This study also advances the implementation science field methodologically. Unlike earlier trials conducted by our team in peri-urban Nepal, which demonstrated the effectiveness of sharing tasks with CHWs in managing hypertension, diabetes, and smoking cessation separately, this trial adopts a more realistic, integrated approach. CHWs will screen, counsel, and refer high risk individuals with any of these three conditions during home visits. This mirrors how CHWs are increasingly expected to work in real-world settings—efficiently delivering care for multiple chronic conditions during routine visits, in addition to tasks related to other conditions (e.g. maternal and child health) and administrative duties. Thus, this study is designed as an effectiveness trial rather than an efficacy trial, with implementation occurring across a large city and under routine program conditions. As such, it will allow for evaluation of outcomes in a less controlled environment, offering more generalizable evidence. This transition from tightly monitored settings to broader program conditions is essential for understanding how task-sharing with CHWs can function when scaled through routine government platforms.

A further strength of this trial is its integration within a type 2 hybrid effectiveness-implementation research study design. Most CHW trials to date have focused solely on assessing clinical outcomes without systematically evaluating how interventions were delivered, how acceptable and appropriate interventions were, and how sustainable interventions could be. Our study is designed to simultaneously examine both effectiveness and implementation outcomes—including acceptability, appropriateness, reach, adoption, fidelity, implementation, sustainability, and cost—using the Consolidated Framework for Implementation Research (CFIR) and its Outcomes Addendum framework. These implementation outcomes are critical for informing the scalability of integrated NCD care models through CHWs in Nepal and similar LMIC settings. It will allow us to estimate population-level impact by assessing reach and effectiveness in the realistic settings and also help identify contextual factors that influence implementation success, which is particularly important for interventions operating across diverse urban neighborhoods. This study will provide policymakers with actionable data on the value and scalability of integrated CHW-led models for urban NCD control in Nepal and similar settings. In addition, this trial incorporates a digital health intervention, including weekly text messages tailored to participants’ risk profiles. These mHealth strategies aim to reinforce CHW-delivered counseling and improve adherence to lifestyle changes or medication. The use of mobile phones as an adjunct to task-sharing could offer a scalable, low-cost tool to support behavior change in LMICs, particularly in urban populations with growing mobile penetration. This design acknowledges the realities of resource-limited health systems, where physician shortages and resource constraints necessitate innovative models for essential health care delivery.

Finally, beyond clinical effectiveness, this trial will generate important operational insights. These include strategies for recruiting and retaining CHWs in urban areas, training them to manage multiple NCDs simultaneously, and sustaining motivation through supervision, incentives, and integration within the health system. It will also shed light on challenges such as navigating private sector dynamics, engaging hard-to-reach populations, maintaining data quality across a larger geographic area, and leveraging digital tools for behavior change communication. The SCALE-NCD study will not only generate robust evidence on effectiveness and implementation outcomes but also guide future adaptations and policy-level decisions for community-based NCD programs.

## Figures and Tables

**Figure 1 F1:**
[figure not shown]
Map of the Pokhara Metropolitan City area

**Figure 2 F2:**
[figure not shown]
CONSORT flow chart

**Figure 3 F3:**
[figure not shown]
Study timeline

**Table 1: T2:** Key components of SCALE NCD interventions and the FCHV training

Key components of SCALE-NCD intervention	
**FCHV home visit** First visit between 0–1 month. Second visit between 4–5 months For 30 mins/visit	**Screening and measurements** Resting BP (digital BP devices) Fasting blood glucose (finger prick) Smoking status assessment
	**Brief motivational interview-based health counseling** Healthy diet Salt intake reduction (<5g/day) o Higher vegetable and fruits intake Weight loss (BMI within 18.5–24.9 kg/m2) Physical exercises (mid-high intensity >150 min/week) Avoidance of harmful alcohol intake (<1 standard drink/day) Smoking cessation Identification and approach to social determinants
	**Medication adherence** Current adherence status
	**Referral of high-risk individuals** BP ≥140/90 mmHg Finger prick blood glucose ≥126 mg/dL
**Mobile phone messages** Once/wk. 10 am	**Individually tailored health education** Advice on healthy diet, exercise, smoking cessation, harmful use of alcohol

## Data Availability

The final trial dataset will be made available as appropriate from the corresponding author on reasonable request.

## Abbreviations

BP: Blood Pressure
CVD: Cardiovascular Disease
c-RCT: Cluster Randomized Controlled Trial
COV: Coefficient of Variation
CHW: Community Health Worker
CFIR: Consolidated Framework for Implementation Research
DSMB: Data and Safety Monitoring Board
FCHV: Female Community Health Volunteer
HIPAA: Health Insurance Portability and Accountability Act
HbA1c: Hemoglobin A1c
HDL: High-density Lipoprotein
IRB: Institutional Review Board
ICC: Intra-class Correlation Coefficient
JHSPH: Johns Hopkins Bloomberg School of Public Health
LMIC: Low- and Middle-income Country
LDL: Low-density Lipoprotein
NeDS: Nepal Development Society
NHRC: Nepal Health Research Council
NCD: Non-communicable Disease
NGO: Non-governmental Organization
REDCap: Research Electronic Data Capture
SMS: Short Message Service
SBP: Systolic Blood Pressure
TAB: Technical Advisory Board
WHO: World Health Organization
